### Data collection and outcomes

#### Procedures and data collection

All staff of the respective trial sites have been trained on the study protocol, informed consent and assessment data collection procedures. A data collection training manual has been developed to guide research staff through step-by-step administration of informed consent and data collection procedures. Assessments are completed in person at baseline and at 12 weeks (Figure 
1).

Potential participants complete a brief screening, either in person or by telephone. During the screen, an in-person baseline interview is scheduled for eligible participants. Informed consent is obtained before the interview, and all questionnaires are interviewer-administered. Most baseline and follow-up interviews are conducted at the intervention site, but some are conducted in the patients’ home.

Baseline descriptive demographic information is collected on health and medical history; venous history and previous ulcer characteristics, clinical status, functional and general health status. A VaLUE questionnaire is administered at baseline and week 12, which collects data related to the social-cognitive constructs which underpin the intervention and to assess self-efficacy, outcome expectations, and a range of dimensions related to health outcomes as shown in Table 
2. A functional assessment is conducted only at baseline and week 12, including: range of ankle motion and a balance and walking measure. Wound data for each participant is collected by the respective clinical staff fortnightly at each site; measures such as ulcer area and the skin integrity are documented. Clinical staff at all sites have been trained in data collection for the study for consistency of data collection. Data related to intervention delivery is tracked by the first author following each call. This includes data on call outcomes (call completion versus missed calls), call duration, call content (via a checklist of topics) and self-reported data on exercise adherence.

**Table 2 T2:** Study procedures for both intervention and control group

**Measure**	**Week**						
	**0**	**1**	**2**	**4**	**6**	**8**	**12**
Clinical history	×						
Sociodemographic data	×						
** *Wound healing* **							
Pressure Ulcer Healing Score (PUSH)	×		×	×	×	×	×
Ulcer characteristics, level of compression	×		×	×	×	×	×
** *Physical activity outcomes* **							
Yale Physical Activity Survey	×						×
Adherence to exercise program	×	×	×	×	×	×	×
Pedometer		×	×	×	×	×	×
** *Functional outcomes* **							
Lawton Instrumental ADL	×						×
Tinetti Gait and Balance Test	×						×
Ankle Range of motion	×						×
**Psychosocial beliefs toward exercise**							
Exercise Self-efficacy Scale	×						×
Outcome expectancies for exercise	×						×
Fear avoidance beliefs for exercise	×						×
** *Health-related quality of life* **							
The MOS Social Support Survey	×						×
The Medical Outcomes Study (MOS) Pain Measures	×						×
Medical Outcomes Survey Short Form-8 questionnaire (SF-8)	×						×
The Geriatric Depression Scale (GDS)	×						×

### Primary outcome measures

*Incidence of complete wound closure* at the completion of the study (12 weeks after initiation of exercise intervention). Wound photographs and tracings are collected fortnightly or monthly by the wound care nurses via the use of acetate grids and Visitrak for planimetry (Smith & Nephew Medical Limited, Hull, England) to determine: ulcer area and fortnightly percent reduction in area; time to healing; and incidence of complete wound healing. Healing is defined as full epithelialisation of the ulcer which has been maintained for at least two weeks without breakdown. Visitrak has been validated as a reliable measure of ulcer size with high intra-inter reliability
[30]. The Pressure Ulcer Scale for Healing (PUSH)
[31] tool is a standardised method of assessing and monitoring the severity of both pressure ulcers and venous leg ulcers using the following parameters: length, width, amount of exudate and wound bed tissue type to track healing progress over time. The PUSH tool has established psychometric properties, such as validity and sensitivity for venous wounds
[32].

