**Method/design:**

This is a randomised controlled in adults with venous leg ulcers to determine the effectiveness of a self-efficacy based exercise intervention. Participants with venous leg ulcers are recruited from 3 clinical sites in Australia. After collection of baseline data, participants are randomised to either an intervention group or control group. The control group receive usual care, as recommended by evidence based guidelines. The intervention group receive an individualised program of calf muscle exercises and walking. The twelve week exercise program integrates multiple elements, including up to six telephone delivered behavioural coaching and goal setting sessions, supported by written materials, a pedometer and two follow-up booster calls if required. Participants are encouraged to seek social support among their friends, self-monitor their weekly steps and lower limb exercises. The control group are supported by a generic information sheet that the intervention group also receive encouraging lower limb exercises, a pedometer for self-management and phone calls at the same time points as the intervention group. The primary outcome is the healing rates of venous leg ulcers which are assessed at fortnightly clinic appointments. Secondary outcomes, assessed at baseline and 12 weeks: functional ability (range of ankle motion and Tinetti gait and balance score), quality of life and self-management scores.

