### Data analysis

Differences in primary and secondary outcomes between groups will be compared using intention to treat analysis. Once a participant is randomised to a study group, they will be considered a trial participant and analysed according to their allocated group, regardless of missing data for follow ups or the amount of intervention received. Bivariate relationships will be tested with Pearson or Spearman correlations, independent t-tests or Mann–Whitney U tests to examine relationships between the dependent variables and the independent variables or chi square for categorical varibales. Each primary and secondary outcome will be modelled using mixed linear models to determine differences between groups and adjust for potential confounders. Potential confounders such as baseline characteristics, for example disease severity, ulcer size and/or duration etc. will be included and controlled for in the final model. Data analysis will be performed using SPSS v21. Statistical significance will be set at p < 0.05 for all analyses.

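### The protocol does not settle on one primary outcome: several wound measures sit under the primary heading and each may be tested at 5%, while only the proportion healed has a sample size

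*Protocol article*

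**What the plan says.** Four places in the protocol article bear on which outcome is primary.

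- **Abstract, Method/design.** One primary outcome, in the singular: "The primary outcome is the healing rates of venous leg ulcers which are assessed at fortnightly clinic appointments". The secondary outcomes listed there are functional ability, quality of life and self-management; no wound measure is among them.
- **Primary outcome measures.** The heading is plural. The section opens with "Incidence of complete wound closure" at 12 weeks. It then says that photographs and tracings serve to determine "ulcer area and fortnightly percent reduction in area; time to healing; and incidence of complete wound healing". The PUSH tool follows, with exudate and "wound bed tissue type to track healing progress over time" among its features. The Secondary outcomes section contains none of area, percent reduction, time to healing or PUSH.
- **Data analysis.** "Each primary and secondary outcome will be modelled using mixed linear models to determine differences between groups", and "Statistical significance will be set at p < 0.05 for all analyses".
- **Sample size calculations.** 44 per group for a 20% difference in the proportion of healed ulcers, with 80% power at a 5% significance level, raised to 55 per group for 20% loss to follow-up. No other wound measure is used.

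**The concern.** A reader who wants to know which single result decides the trial gets different signals. The sample size and the opening of the outcomes section point to closure at 12 weeks. The abstract's healing rates, tied to fortnightly visits, could equally be the speed of area reduction or a hazard of healing. The plural heading and the phrase about each primary outcome suggest several primary outcomes. A linear mixed model suits repeated area or PUSH scores more naturally than a yes/no closure outcome or a time to healing, so the analysis text does not resolve the matter.

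At stake is what a primary success means. If a favourable result on any one wound measure could be reported as the primary finding, the chance of a false claim exceeds the 5% on which the trial was sized. The openness of the trial makes this more than a formality. The Study design section calls the trial open, and the researcher who makes the coaching calls also reviews wound status, so wound trends by arm may be visible before the analysis.

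**Working it through.** **1. The plan's own figure.** 44 / (1 − 0.20) = 55, so the allowance for loss to follow-up reproduces. The 44 cannot be reproduced uniquely because no control healing proportion is given; that is a separate matter. What counts here is that the calculation concerns one comparison, the proportion healed, at 5%.

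**2. Size of the family.** The document gives no count, so it is an assumption:
- k = 3: closure; area and percent reduction taken as one; time to healing.
- k = 4: the same plus PUSH.
- k = 5: the same, with area and percent reduction counted separately.

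The incidence of complete healing in the list from tracings repeats closure and is not counted again.

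**3. Closure alone is primary.** One test at 0.05 has a false-positive rate of 5%, whatever else is tested alongside it.

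**4. Success on any of k measures, independent tests.** Rate = 1 − (1 − 0.05)^k.
- k = 3: 1 − 0.95³ = 0.143
- k = 4: 1 − 0.95⁴ = 0.185
- k = 5: 1 − 0.95⁵ = 0.226

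**5. Success on any of k measures, correlated tests.** All measures come from the same study ulcer, so independence is not realistic. Take k two-sided z-tests with common correlation ρ, Z_j = √ρ·C + √(1−ρ)·E_j, where C and the E_j are independent standard normal, and count a success if any |Z_j| > 1.96. With 1,000,000 simulated draws under no effect:

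| k | ρ = 0.5 | ρ = 0.7 | ρ = 0.9 |
|---|---|---|---|
| 3 | 12.6% | 10.9% | 8.4% |
| 4 | 15.6% | 13.1% | 9.4% |
| 5 | 18.4% | 14.9% | 10.2% |

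The protocol gives no correlations; these values are assumptions. Across the table the range is 8.4% to 18.4%, and every cell exceeds 5%.

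**The case against.** The strongest reply is that closure is already set apart. It is the only wound outcome in its section that is italicised and given an endpoint time, and it alone drives the sample size. The abstract uses the singular. The list of area, percent reduction and time to healing can be read as a description of what tracings provide, and PUSH is introduced as a tracking tool. On that reading there is one primary outcome and its test has a 5% error rate.

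Much of this stands. A reader might infer that the plan's primary false-positive rate is well above 5% as a matter of fact, or that the 5% in the sample size fails. The document does not support that. The 5% there belongs to the closure comparison, which other tests leave untouched, and nowhere does the protocol say that success on any listed measure suffices. Nor do the secondary questionnaires and functional tests add to the error of a primary claim. The lack of a multiplicity method is not a fault in itself, because the analysis plan is not shown and an article commonly leaves this to it. That the primary outcome will be picked after seeing the data cannot be shown either; the protocol reports prospective registration, and the registry record is not available here.

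The reply does not remove the labelling problem. The primary heading is the only classification the article gives to the non-closure wound measures, the analysis text speaks of each primary outcome, and healing rates has more than one meaning.

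**Conclusion.** The point holds as an unclear primary outcome, with a conditional effect on error. Followed as written, the plan permits several wound measures to be tested as primary, each at 5%, although only one was used to size the trial. If closure alone is primary, the rate is 5%. If any of three to five measures may be called primary success, it is about 8% to 18% at assumed common correlations of 0.9 to 0.5. The independence values of 14% to 23% are upper values, since the measures overlap heavily: percent reduction derives from area, closure by 12 weeks is time to healing cut at that point, and PUSH includes length and width. The result rests on the assumed family size, the assumed correlations and an any-measure success rule that the protocol neither states nor rules out. This should be settled before analysis.

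**What to change.** By a dated amendment made before the data are analysed:

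- Name the incidence of complete closure of the study ulcer at 12 weeks, under the protocol's existing healing definition, as the sole primary outcome, tested at 5%.
- Move time to healing, ulcer area or percent reduction, and PUSH to the secondary outcomes, reported as supportive estimates with 95% confidence intervals.
- Replace healing rates in the abstract with the same outcome, and put the heading and the analysis sentence in the singular where they refer to the primary outcome.

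Alpha, sample size and data collection do not change. The cost is the amendment, with a stated reason because the trial is open and already in follow-up, and that the other wound measures can no longer be claimed as primary.

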### Randomisation and blinding

After completing all baseline data collection measures, participants are randomised to either intervention group protocols or control group protocols for 12 weeks or until healed. Participants in the intervention group receive evidence based wound care, and a VaLUE pack which includes a pedometer, general advice for looking after their legs and an information sheet. In addition those in the intervention group receive an instructor developed exercise booklet ‘VaLUE your Independence’, along with a verbal explanation and demonstration of the resistance exercise program. Those in the intervention are followed up by the first author for telephone exercise coaching at week one, two, four, six eight and twelve. Participants in the control group will also receive a VaLUE pack which includes a pedometer and the same general advice information sheet for looking after your legs.

The randomisation schedule has been prepared by an assistant independent to the research project using a computer generated random numbers table. To conceal randomisation, the independent staff member prepared consecutively numbered, sealed, opaque envelopes for each site. The envelopes are kept in a locked location at each site accessible only by an unblinded researcher. As VaLUE is a self-administered intervention, blinding of the participant and the researcher who conducts the telephone follow-up is by necessity unblinded.

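### Healing needs two weeks of maintained closure, but the primary outcome is read at week 12 with no later wound assessment described, so the endpoint is in effect confirmed closure by week 8 to 10, depending on which schedule a site follows

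*Protocol article*

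**What the plan says.** Under Primary outcome measures, the protocol article sets the incidence of complete closure "at the completion of the study (12 weeks after initiation of exercise intervention") as the primary outcome. The same paragraph adds the maintenance condition: "Healing is defined as full epithelialisation of the ulcer which has been maintained for at least two weeks without breakdown". Time to healing is to be derived from the same wound data.

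Participation is limited under Randomisation and blinding: "participants are randomised to either intervention group protocols or control group protocols for 12 weeks or until healed". No wound assessment later than week 12 appears anywhere in the article.

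The timing of wound assessments is given in three ways:

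- **Table 2.** The wound-healing rows, including "Ulcer characteristics, level of compression", are marked at weeks 0, 2, 4, 6, 8 and 12. The table has no week 10 column and nothing after week 12.
- **Abstract and Procedures and data collection.** The abstract speaks of "healing rates of venous leg ulcers which are assessed at fortnightly clinic appointments", and the data collection text agrees: "Wound data for each participant is collected by the respective clinical staff fortnightly at each site".
- **Primary outcome measures.** "Wound photographs and tracings are collected fortnightly or monthly by the wound care nurses".

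**The concern.** A definition that requires two weeks of maintained closure needs an observation at least two weeks after the first closed one. If the last described observation falls at the outcome time point, closures first seen there have no confirming visit. Each such ulcer must then be handled in one of two ways. It can be counted as not healed, which discards closures that may be genuine. Or it can be counted as healed, which departs from the protocol's own definition. The article does not say which.

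Because the schedules differ, the cut-off for a confirmable closure also differs between sites that follow different parts of the text. Time to healing has the same weakness, since the gap between observations is two weeks on one reading and four on another. The phrase limiting participation to 12 weeks or until healing adds a further doubt: it does not say whether observation continues through the two-week maintenance period once an ulcer has closed.

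**Working it through.** **Plan's own figures.** No stated figure is disputed here. The related ones are the 20-point target difference at 12 weeks and 44 participants per group, raised to 55 for 20% loss: 44 / (1 - 0.20) = 55, which reproduces. The control healing rate is not stated, so any rate used below is an assumption.

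**Step 1: visit calendar.** A closure first seen at visit *v* can be confirmed by week 12 only if some later visit *u* satisfies *u* - *v* ≥ 2 and *u* ≤ 12.

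| Schedule | Visits (weeks) | Last confirmable first sighting | Confirmed at |
|---|---|---|---|
| Table 2 | 0, 2, 4, 6, 8, 12 | week 8 | week 12 |
| Monthly tracings | 0, 4, 8, 12 | week 8 | week 12 |
| Fortnightly text | 0, 2, 4, 6, 8, 10, 12 | week 10 | week 12 |

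On all three, a first sighting at week 12 has no confirming visit.

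**Step 2: illustration of size.** Assume a constant healing hazard, no re-opening, and 12-week closure proportion *p* in an arm. Closure by week *w* is F(*w*) = 1 - (1 - *p*)^(*w*/12). With a 20-point difference at week 12:

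| Assumed at week 12 | By week 8 | Difference | By week 10 | Difference |
|---|---|---|---|---|
| 30% vs 50% | 21.2% vs 37.0% | 15.8 | 25.7% vs 43.9% | 18.2 |
| 40% vs 60% | 28.9% vs 45.7% | 16.8 | 34.7% vs 53.4% | 18.7 |
| 50% vs 70% | 37.0% vs 55.2% | 18.2 | 43.9% vs 63.3% | 19.5 |
| 60% vs 80% | 45.7% vs 65.8% | 20.1 | 53.4% vs 73.8% | 20.4 |

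Differences are taken before rounding.

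**Step 3: share of 12-week closures that could not qualify, at 50% vs 70%.**

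- Week 8 cut-off: (50.0 - 37.0) / 50.0 = 26% in control and (70.0 - 55.2) / 70.0 = 21% in intervention.
- Week 10 cut-off: (50.0 - 43.9) / 50.0 = 12% in control and (70.0 - 63.3) / 70.0 = 10% in intervention.

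With 44 evaluable per group, the week 8 cut-off affects 44 × 0.130 = 5.7 and 44 × 0.148 = 6.5 participants, about 12 in all. The week 10 cut-off affects 44 × 0.061 = 2.7 and 44 × 0.067 = 2.9, about 6 in all. The absolute loss is similar in the two arms, which is why the difference moves little.

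**The case against.** Several points on the other side have force.

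- **Week 8 is not the only cut-off.** A reader of Table 2 might infer that closures after week 8 can never count. The documents do not support that. The abstract and the data collection text both describe fortnightly assessment, under which a closure seen at week 10 is confirmable at week 12. Table 2's columns are baseline plus the coaching-call weeks, so the absent week 10 may be a matter of layout. Even on Table 2, an ulcer that closes in week 9 may truly stay closed for two weeks by week 12; the table simply offers no visit to document it. This stands, and is why the cut-off is given as week 8 to 10.
- **Monthly tracing can confirm healing.** A reader might infer that it cannot. The definition asks for at least two weeks, so an ulcer closed at week 4 and still closed at week 8 meets it.
- **Assessor blinding is not described.** Because the trial is open, a reader might infer that unblinded staff would decide how late closures count. The article names only the participant and the telephone researcher as unblinded. It does not give the status of those who assess or classify wounds.
- **The article is condensed.** How late closures are adjudicated could sit in a fuller document, and no sentence says that clinic observation stops at week 12. This stands in part. But the definition, the time point and the conflicting schedules are all stated here, and they do not fit together. An analysis plan can supply a counting rule; it cannot supply an observation that was never collected.
- **The effect on the difference is small.** The rule applies equally to both arms, and the calculation shows dilution at most, not bias. This stands.

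**Conclusion.** The point holds. As written, the primary outcome cannot be applied at its own time point to ulcers first seen closed at week 12, and the schedules conflict on which earlier closures can be confirmed. The effective endpoint is confirmed closure by week 8 (Table 2 or monthly tracing) or by week 10 (fortnightly text).

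Under a constant hazard and 50% vs 70% at week 12, about a quarter to a fifth of 12-week closures (week 8) or about a tenth (week 10) are left without a clear classification. The effect on the target difference is modest and depends on the assumed rates. Over the range examined, 20 points becomes about 16 to 20 with a week 8 cut-off and about 18 to 20 with a week 10 cut-off, with no shrinkage at 60% vs 80%. The visit-calendar result rests only on the stated text. The percentages rest on assumed rates and an assumed hazard shape. Because the ambiguity affects the primary outcome, it should be settled before any comparison by arm.

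**What to change.** 1. Reconcile Table 2, Procedures and data collection, and Primary outcome measures to one wound-assessment schedule, the same in both arms: fortnightly including week 10, as the abstract and the data collection text already say.
2. Before any comparison by arm, define the primary outcome as closure first observed on or before week 12 and confirmed at the next routine clinic assessment at least two weeks later. For ulcers first seen closed at week 12, take the confirmation from the clinic record where available.
3. State in advance how week 12 closures without a confirmation are counted, and report the alternative count as a sensitivity analysis.
4. Date healing at the first closed observation, and state that wound observation continues through the two-week maintenance period after closure.

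The cost is one further data item for ulcers first seen closed at week 12, plus text changes. Where tracing is monthly in practice, moving to fortnightly is a real change in data collection for participants still under observation. The article gives the trial's status as in follow-up, so some confirmations may be unavailable for participants already past week 12; the rule in item 3 covers them.
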